### Primary outcome measures

As in previous research by our team, the primary outcome measure for the study is the change in SADQ score at 6 months post randomisation. The SADQ is a short 20-item questionnaire designed to measure severity of dependence on alcohol [40]. There are five subscales with four items in each: Physical Withdrawal, Affective Withdrawal, Withdrawal Relief Drinking, Alcohol Consumption, and Rapidity of Reinstatement. Each item is scored on a 4-point scale, ranging from "Almost Never" to "Nearly Always" resulting in a corresponding score of 0 to 3. Thus the total maximum score possible is 60 and the minimum is 0.

### Secondary outcome measures

The secondary outcome measures are:

1. A change in AUDIT score from baseline at 12 weeks and at 6 months post randomisation. Although AUDIT is a screening test for alcohol use disorders [41], in common with other studies, we will in this context use it as both an outcome measure and a pre-screen to establish presence of alcohol dependence. The sum of the items scored has been used in several studies to indicate dependence and therefore will allow for comparability with other trial baseline and outcome measures [10].

2. Measure of alcohol dependence utilising the Leeds Dependency Questionnaire (LDQ) [42] at baseline, 12 weeks and 6 months post randomisation. The LDQ is a 10-item questionnaire designed to measure dependence upon a variety of substances including alcohol. The questionnaire includes 1 item from 10 markers that define dependence; these include pre-occupation, salience of alcohol, compulsion to start, planning around alcohol consumption, maximize effect, narrowing of use of repertoire, compulsion to continue, primacy of effect, constant state and cognitive set. Each item is scored 0-1-2-3, giving a maximum of 30 with higher score indicating greater degree of dependence.

3. Quantity and frequency of alcohol consumption in UK units per drinking day at baseline, 12 weeks and 6 months post randomisation.

4. Readiness to Change Questionnaire (RCQ) at baseline, 12 weeks and 6 months post randomisation. This is an important measure for non-treatment seeking populations as it has been demonstrated that treatment-seeking is an indication of treatment readiness, which has been seen as important in achieving treatment outcomes [20]. Using this measure will help us to investigate if treatment readiness does indeed have any bearing on treatment outcome in the population and setting.

5. Number of ED attendances 6 months pre and 6 months post treatment/control.

6. Hospital length of stay sum days in hospital 6 months pre and 6 months post randomisation.

7. Number of hospital admissions 6 months pre and 6 months post randomisation.

8. Length of stay for initial treatment in days.

9. Biochemical indicators of co-morbid conditions including Gamma-glutamyl transferase (GGT), Alanine aminotransferase (ALT) and mean corpuscular volume (MCV), when available will be extracted from a recent laboratory records; this is defined as the last available value prior to randomization.

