### Evidence for effectiveness of treatment in acute care settings

When considering brief intervention (BI) as a treatment approach for alcohol dependence in an acute care setting, it is important to note that the intensity of intervention does not seem to be a predictor of treatment effectiveness [11-15]. For that reason, brief treatments may be as effective as more intensive treatments in some patient groups. It is therefore noteworthy that, for those patients who are dependent on alcohol, treatments that are brief, timely and pragmatic have received little research focus. Furthermore, the assessment of the effectiveness of treatment is complex; particularly since between 12 to 35% of patients recover with little or no specialist intervention, a phenomenon described as "natural recovery" [16-19]. It has also been established that irrespective of their similarities and differences treatments seem to perform equally well, or badly [20,21].

It is well established that brief treatments are effective for hazardous and harmful drinkers [22] but may also have some efficacy in alcohol-dependent patients [22-30]. However, BI as a treatment option in acute hospitals has yet to be systematically tested in dependent drinkers [31-34]. The ED has been shown to be an appropriate setting in which to identify non-treatment seeking hazardous and harmful drinkers [31,35], and is potentially best placed to deliver effective care based on a BI approach [22,23,25-29,35,36]. However, to date, there has been little focus on the effectiveness of BI in alcohol dependence. A pragmatic non-randomised controlled study (Quaisi-experimental) of BIs by ASNs showed that 30% of alcohol-dependent patients' maintained abstinence for 6 months post treatment [37]. A subsequent study showed that patients treated by the ASN had significantly shorter stay in hospital and a significant reduction in alcohol consumption and dependence at 6 months [38]. Furthermore, a recent retrospective evaluation found that alcohol dependent patients realised as much benefit as non-dependent patients from BIs delivered by an ASN in acute care [35].

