## Methods/Design

### Hypothesis

EBIs delivered to alcohol-dependent patients in a hospital setting by an ASN will be effective when compared to usual care in reducing overall alcohol consumption and improving on the standard measures of alcohol dependence.

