### Overall aim of the study

To test the clinical and cost effectiveness of extended BI for individuals with alcohol dependence in an acute hospital setting.

The study objectives are:

1. To determine whether BI reduces overall alcohol consumption.

2. To determine whether BI is effective in the treatment of alcohol dependence.

3. To determine whether BI reduces the length of stay in hospital

4. To determine how patients feel about being approached in an opportunistic manner for screening for alcohol-related problems and subsequently being asked to be part of a research trial.

5. To determine the cost effectiveness of BI for alcohol dependence

The study is a randomized controlled trial. The study has been approved by North West Research Ethics Committee ref: 09/H1005/61, and is fully compliant with the Helsinki declaration 2008.

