### Analysis of secondary outcomes

The AUDIT and AUDIT-C, LDQ and RCQ scores will be summarised using descriptive statistics: means with 95% confidence intervals (or medians with inter-quartile ranges if non-normally distributed) at baseline, 12 weeks and 6 months. Change from baseline at 12 weeks and at 6 months post treatment will be presented. The hypothesis of no difference between the two treatment arms at 12 weeks and 6 months (separate analyses) will be tested using analysis of covariance (ANCOVA), controlling for baseline measurements. A p-value of 0.05 (5% level) will be used to declare statistical significance and 95% confidence intervals of the estimated effects will be reported. Time by treatment interaction will be assessed. This analysis using ANCOVA will not adjust for any missing data. However, reasons for missing outcome data will be reported and a sensitivity analysis will be undertaken Time by treatment interaction will be assessed. The mean (standard deviation) or median (inter-quartile range) of quantity and frequency of alcohol consumed in UK units per drinking day will be computed depending on whether it is skewed or not, and compared across treatment groups at 12 weeks and at 6 months post treatment using a t-test or Mann Whitney U test. The number of ED attendances is also similarly analysed. Summaries of length of stay in hospital will be presented as means (standard deviations) or medians (inter-quartile ranges) depending on whether it is normally distributed or not, and compared across treatment groups. Laboratory parameters will be summarized using means, standard deviations, confidence intervals, and ranges. Additional summaries of the data included plots of mean (±SE) values over time and scatter plots of pre- vs. post-treatment values. Change from baseline and at 12 weeks and at 6 months post treatment will be presented. A formal test of a treatment-covariate interaction will be conducted by including the interaction term in a regression model. Exploratory analysis will be conducted as to the impact on any treatment effect of other factors such as gender or age. A p-value of 0.05 (5% level) will be used to declare statistical significance and 95% confidence intervals of the estimated effects will be reported.

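### The consumption outcome is stated and analysed as units per drinking day, which does not directly measure the overall consumption named in objective 1 and the hypothesis

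*Protocol article*

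**What the plan says.** In the protocol article, the Hypothesis section states that the extended brief intervention (EBI) "will be effective when compared to usual care in reducing overall alcohol consumption and improving on the standard measures of alcohol dependence". Objective 1, under Overall aim of the study, is "To determine whether BI reduces overall alcohol consumption".

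The outcome that answers to this is item 3 of Secondary outcome measures: "Quantity and frequency of alcohol consumption in UK units per drinking day at baseline, 12 weeks and 6 months post randomisation". Analysis of secondary outcomes keeps the same unit. It says that the mean or median of "quantity and frequency of alcohol consumed in UK units per drinking day will be computed depending on whether it is skewed or not", and that the variable will be "compared across treatment groups at 12 weeks and at 6 months post treatment using a t-test or Mann Whitney U test".

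The Abstract lists quantity and frequency of consumption as a secondary outcome without giving a unit. No section names total units over a week or month, number of drinking days, or abstinence rate as an outcome.

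Three other statements bear on the point:
- The Background reports an earlier non-randomised study of brief intervention by alcohol specialist nurses in which "30% of alcohol-dependent patients' maintained abstinence for 6 months post treatment".
- The description of the intervention includes advice to reduce drinking or to stop.
- Planned Analysis applies intention to treat to every analysis, with all patients kept as randomised.

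**The concern.** The label of item 3 names two things, quantity and frequency, but the unit attached to it carries only one. Units per drinking day is how much a patient drinks on a day when he or she drinks. Overall consumption also depends on how many such days there are, and the tested variable leaves that out. A patient who drinks on fewer days, at the same intensity, has reduced overall consumption and registers no change.

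The second difficulty is abstinence. A patient with no drinking days in the recall period has no units per drinking day, only a ratio of zero to zero. Abstinence is one of the results the intervention may aim for, so the case will not be rare. The value must be either missing or set to zero. If it is missing, the comparison is confined to patients still drinking. That is a state reached after randomisation which treatment may change, and the restriction would not fit the intention-to-treat statement.

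At stake is the answer to the first-named objective. A real fall in overall consumption could appear as no difference, or even as a rise.

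**Working it through.** The protocol gives no effect size, standard deviation or power for consumption, so there is no planned figure to reproduce. The check uses an identity and then illustrations on assumed inputs.

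**Identity.** For one patient over a fixed period:

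total units = drinking days × units per drinking day, so units per drinking day = total units ÷ drinking days.

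With no drinking days this is 0 ÷ 0. The total is then simply 0.

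**1. Fewer drinking days, same intensity (assumed inputs).**
- 15 units per drinking day, 6 versus 3 days a week: 15 × 6 = 90 and 15 × 3 = 45 units a week, a 50% fall. Units per drinking day: 15 versus 15.
- 20 units per drinking day: 20 × 6 = 120 and 20 × 3 = 60, again a 50% fall with no change per drinking day.

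The starting intensity does not matter. Any change confined to drinking days is invisible in this unit.

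**2. How many patients would have no defined value.** Inputs: 30% abstinence from the Background study, and 51 or 65 evaluable patients per arm from the two calculations under Sample Size calculation.
- 0.30 × 51 = 15.3, about 15.
- 0.30 × 65 = 19.5, about 20.

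These counts hold only if abstainers are not scored 0 and if the 30% carries over to this trial.

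**3. Effect of abstinence on the two measures.** Assume that everyone still drinking has 20 units on 6 days a week, that is 120 units a week, in both arms. EBI abstinence is 30%. The protocol gives no control-arm abstinence rate, so 12% is assumed.
- Mean total, all patients: control 0.88 × 120 = 105.6; EBI 0.70 × 120 = 84.0. Ratio 84.0 ÷ 105.6 = 0.795, about 20% lower.
- Units per drinking day, drinkers only: 20 versus 20, no difference.
- Range: with EBI abstinence of 25% to 35% and control at 12%, the fall in the total is 15% to 26%. With control at 25% and EBI at 30%, it is 1 − 84.0 ÷ (0.75 × 120) = 1 − 84.0 ÷ 90.0, about 7%. With equal abstinence it is nil.

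**4. Simulation of the same situation.** Assumed: units per drinking day lognormal, median 18, log standard deviation 0.5, the same in both arms; abstinence 12% versus 30%; Mann-Whitney test, two-sided 5%; 4,000 runs.

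| Rule for abstainers | 51 per arm | 65 per arm |
|---|---|---|
| Left out | rejects in 4.5% | rejects in 3.9% |
| Scored 0 | rejects in 34% | rejects in 43% |

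Leaving abstainers out gives roughly the null rate although total consumption differs. Scoring them 0 recovers part of the signal.

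**5. Possible reversal.** With the same distribution, mean units per drinking day is 20.4. If the lightest 30% of drinkers stop, the mean among those left is 24.6. With zeros included it is 17.2. The same benefit reads as a rise or a fall according to the rule used.

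**The case against.** Four arguments can be made for the plan as written.

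**The outcome is called quantity and frequency.** The unit may have been meant for quantity only, with frequency reported beside it. A reader might infer from the stated unit that objective 1 is not tested at all. The documents do not support that: the label, in the Abstract and in item 3, implies that frequency is recorded, so a total could be derived. What stands against the plan is that the analysis section treats this as one variable in one unit, and the total is nowhere defined.

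**Other planned measures touch on consumption.** AUDIT and AUDIT-C are compared between arms by ANCOVA, and the SADQ contains an Alcohol Consumption subscale. These are relevant, but they are scores rather than volumes. No separate analysis of the subscale is stated, and nothing links any of them to objective 1.

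**Nothing says that abstainers are dropped.** This is correct. A reader might infer that the best responders fall out of the comparison, but no section excludes them and the intention-to-treat statement points the other way. Scored 0, they would take the lowest ranks in the Mann-Whitney test and nothing would condition on continued drinking. The selection argument is therefore conditional.

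**A zero rule belongs in an analysis plan.** Agreed; its absence from a condensed article is not a fault in itself. The stated unit is a different matter. A later zero rule would make the variable computable for everyone, yet it would still miss a fall in drinking days.

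The sizes shown are also illustrations. The 30% comes from a non-randomised study, and the intensities, drinking days and control abstinence are assumed.

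**Conclusion.** The point holds in a limited form. Overall consumption is the first half of the hypothesis and objective 1, and it is not directly measured by the consumption outcome as worded. The unit is given twice, in the outcome list and in the analysis, and it captures only intensity on drinking days. This is a mismatch between objective and stated measure rather than a missing detail.

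The blindness to drinking days follows from the definition and needs no assumption; a halving of drinking days halves the total and leaves the tested variable unchanged. The trouble with abstainers depends on how they are handled. If they were left out and the 30% applied, about 15 of 51 or 20 of 65 evaluable EBI patients would be affected. The 20% difference in total consumption that a drinkers-only comparison would miss rests on the assumed 12% versus 30% abstinence and shrinks as the two rates converge.

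The consequence is confined to one of nine secondary outcomes. The primary outcome and the sample size rest on the SADQ and are unaffected. The change is worth making because this is the only unit-based outcome for the first-named objective.

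**What to change.** In item 3 of Secondary outcome measures and in Analysis of secondary outcomes, define the consumption outcome as total UK units over a fixed recall period, for example per week as units per drinking day × drinking days per week. Score patients with no drinking days 0, and include all patients with follow-up data in the arm to which they were randomised. Report drinking days, and units per drinking day among those still drinking, as descriptive components without a between-arm test.

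The cost is a change of wording and derivation, provided that drinking frequency is recorded, as the outcome's label implies. If the case report form does not record it, a frequency question over the same recall period has to be added. The total will be skewed with a cluster of zeros; the Mann-Whitney option already in the plan can handle that. No change to the primary outcome or sample size is needed.

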### Sample Size calculation

Based on a previous study by ourselves on dependent drinkers receiving interventions from an ASN, it is expected that 55% of such patients will display a fall in SADQ score between baseline and 12 weeks' follow up [38]. Another confounder in this area of research is the phenomenon of natural recovery (NR). The NR rate over this time period expected in the control group is expected to be no more than 25% (the literature ranges from 12% with a treatment population [40] up to 35% within a general lifetime population [43,44]). In order to detect this difference between the groups (55% vs. 25%) with 90% power at the 5% significance level, approximately 65 patients are required in each group. In order to allow for an estimated 50% drop out rate (observed in previous studies in similar patients), 130 patients will be recruited per group. It is estimated that at least 5 eligible patients will be recruited per week, and thus this target should be achieved within the 12 month recruitment period.

A fall in SADQ at 6 months is be the primary outcome. As there were few studies that report SADQ scores at baseline and follow-up, the revised power calculation was based on the our own studies that 22% vs 53% fall in SADQ between control and Intervention arms at 6 months. In order to detect this difference between the groups (55% vs. 25%) with 90% power at the 5% significance level, the required size is 103 (51 per group), and 206 (103 per group) once adjusted for 50% dropout.

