**Methods/Design:**

This is a randomised controlled trial with a primary hypothesis that extended brief interventions (EBI) delivered to alcohol-dependent patients in a hospital setting by an Alcohol Specialist Nurse (ASN) will be effective when compared to usual care in reducing overall alcohol consumption and improving on the standard measures of alcohol dependence. Consecutive patients will be screened for alcohol misuse in the Emergency Department (ED) of a district general hospital. On identification of an alcohol-related problem, following informed written consent, we aim to randomize 130 patients per group. The ASN will discharge to usual clinical care all control group patients, and plan a programme of EBI for treatment group patients. Follow-up interview will be undertaken by a researcher blinded to the intervention at 12 and 24 weeks. The primary outcome measure is level of alcohol dependence as determined by the Severity of Alcohol Dependence Questionnaire (SADQ) score. Secondary outcome measures include; Alcohol Use Disorders Identification Test (AUDIT) score, quantity and frequency of alcohol consumption, health-related quality of life measures, service utilisation, and patient experience. The trial will also allow an assessment of the cost-effectiveness of EBI in an acute hospital setting. In addition, patient experience will be assessed using qualitative methods.

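### The sample-size section leaves two recruitment targets, 260 and 206, unreconciled, and labels the revised calculation with rates other than those it announces

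*Protocol article*

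**What the plan says.** Under Sample Size calculation, the first paragraph assumes that "55% of such patients will display a fall in SADQ score between baseline and 12 weeks' follow up" in the intervention arm, and sets the control rate at no more than 25% on grounds of natural recovery. For 55% vs 25%, 90% power and 5% significance it concludes that "approximately 65 patients are required in each group". Allowing for 50% dropout, it recruits 130 per group, which is 260 in total.

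The second paragraph names the 6-month fall in SADQ as the primary outcome and presents a calculation that it calls revised. The new assumption is "22% vs 53% fall in SADQ between control and Intervention arms at 6 months". The next sentence, however, gives the difference to be detected as "the groups (55% vs. 25%) with 90% power at the 5% significance level, the required size is 103 (51 per group"), and inflates this to 206 in total, or 103 per group, for 50% dropout.

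The Methods/Design part of the abstract says "we aim to randomize 130 patients per group". Under Planned Analysis, an internal pilot after 160 randomised patients compares the 12-week proportion with a fall in SADQ against the original sample size calculation. It may lead to increased recruitment on the steering committee's advice.

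**The concern.** Three things do not fit together.

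- As printed, one set of inputs (55% vs 25%, 90% power, 5% significance) is given two sizes: about 65 and 51 per group.
- The revised paragraph announces one pair of rates and prints another beside its result.
- Targets of 130 and 103 per group both stand. No sentence says which one governs, and the abstract carries only the larger.

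The recruitment target and its power claim are figures that the trial relies on. As written, recruitment could end at 206 or at 260 with 90% power claimed for either. The steering committee would also not know which target, or which pair of rates, the internal pilot is meant to adjust.

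**Working it through.** **Inputs.** Rates of 55% vs 25% and 53% vs 22%, 90% power, 5% significance and 50% dropout come from Sample Size calculation. Equal allocation comes from Trial randomization procedure. The section does not state sidedness or the test. I assume a two-sided test (z = 1.960 for significance, 1.2816 for power) and show several formulas. I read the 22% and 53% as proportions of patients with a fall, as in the first paragraph.

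**Dropout inflation.** 65/0.5 = 130 per group, and 103/0.5 = 206 in total. Both agree with the article. A total of 103 is 51.5 per group, so 51 is that figure rounded down.

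**Size per group.** With difference d and mean rate p̄, let V0 = 2p̄(1−p̄) and V1 = p1(1−p1) + p2(1−p2).

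- Pooled: n = (1.960√V0 + 1.2816√V1)²/d²
- Unpooled: n = V1(1.960 + 1.2816)²/d²
- Continuity-corrected: n' = (n/4)(1 + √(1 + 4/(nd)))², with n from the pooled formula

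For 55% vs 25%: d = 0.30, V0 = 2 × 0.40 × 0.60 = 0.480, V1 = 0.2475 + 0.1875 = 0.435.
For 53% vs 22%: d = 0.31, V0 = 2 × 0.375 × 0.625 = 0.46875, V1 = 0.2491 + 0.1716 = 0.4207.

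| Rates | Pooled | Unpooled | Continuity-corrected |
|---|---|---|---|
| 55% vs 25% | 53.9, so 54 | 50.8, so 51 | 60.4, so 61 |
| 53% vs 22% | 49.1, so 50 | 46.0, so 46 | 55.4, so 56 |

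**The article's 51.** It is close to the pooled result for the announced 53% vs 22% (50). It also equals the unpooled result for the printed 55% vs 25%. The arithmetic therefore cannot settle which pair was used.

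**The article's 65.** None of these formulas gives 65 for 55% vs 25% at 90% power, and the arcsine formula gives 55. At 95% power the pooled and arcsine formulas give 67 and the unpooled formula 63. So 65 is larger than the stated inputs need.

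**Power at the evaluable sizes.** Pooled power is Φ((d√n − 1.960√V0)/√V1).

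- n = 51, 55% vs 25%: (2.1424 − 1.3579)/0.6595 = 1.189, giving 88.3%.
- n = 51, 53% vs 22%: (2.2138 − 1.3419)/0.6486 = 1.344, giving 91.1%.
- n = 65, 55% vs 25%: (2.4187 − 1.3579)/0.6595 = 1.608, giving 94.6%.
- n = 65, 53% vs 22%: (2.4993 − 1.3419)/0.6486 = 1.784, giving 96.3%.

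Fisher's exact test, by enumeration over both binomial distributions:

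| Evaluable per group | Randomised in total | 55% vs 25%: pooled / Fisher | 53% vs 22%: pooled / Fisher |
|---|---|---|---|
| 51 | 206 | 88.3% / 84.7% | 91.1% / 87.7% |
| 65 | 260 | 94.6% / 92.6% | 96.3% / 94.8% |

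**Distance between the targets.** 260 − 206 = 54 patients, and 54/260 = 21%.

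**Which target the rest of the article follows.** At the forecast 5 patients a week, 52 weeks yield 260, so the 12-month recruitment period matches the first target. The internal pilot also refers to the original calculation and to 12 weeks. With equal groups, the overall proportion expected with a fall is (55 + 25)/2 = 40% under the first pair and (53 + 22)/2 = 37.5% under the second.

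**The case against.** The strongest reply is that this is an editing slip. The second calculation is labelled as revised and tied to the 6-month primary outcome. Its reference to the difference points back to the rates just announced, and the pooled formula for those rates gives 50, close to 51. On this reading, 55% vs 25% was carried over from the first paragraph and 206 is the later figure. This is the simplest explanation and may well be right. The article does not establish it, because the unpooled formula for the printed rates gives 51 exactly. It also leaves the abstract, the recruitment forecast and the pilot on the first calculation.

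Three stronger readings are tempting, and the document does not support them.

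- A reader might infer that the same inputs were computed twice with different answers. They are identical only in print; the announced rates and the time points differ.
- A reader might infer that the trial has no valid recruitment number. But 260 gives more than 90% power under either pair of rates, and the second calculation is marked as revised. What is missing is a statement of which governs.
- A reader might see a separate arithmetic error in 103 against 51 per group. It is rounding.

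The internal pilot does not resolve the matter. It contemplates only an increase in recruitment and does not reconcile 206 with 260.

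**Conclusion.** The section contradicts itself on the rates behind the revised calculation and on the recruitment target, and it should be corrected. The consequence is moderate. At 206 randomised with 50% dropout, power is about 91% (Fisher 88%) if 53% vs 22% was meant, and about 88% (Fisher 85%) if 55% vs 25% was meant. The claimed 90% thus holds or falls short by a few points, depending on an input that the text mislabels and on a test that it does not name. At 260 the claim is met with room to spare, because 65 per group is conservative.

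These figures assume a two-sided 5% test, exactly 50% dropout and equal groups. They concern the comparison of proportions on which the article bases its size, not the ANCOVA of scores planned for the primary outcome.

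**What to change.** - State in Sample Size calculation which target governs, 260 or 206, and give the same figure in the abstract.
- If the revised calculation used 53% vs 22%, correct the parenthesis to those rates. If 55% vs 25% was meant, restate the power of 51 per group as about 88% (pooled) or 85% (Fisher).
- Under Planned Analysis, refer the internal pilot check to the governing calculation, with its rates and time point.

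This costs wording only and needs no extra patients beyond the target chosen. The stated power may become slightly less favourable if 206 and 55% vs 25% are kept.
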